### Sample size

According to the SDM Process_4 user guide, Sepucha and Fowler [24] suggest assumptions for the sample size calculations, including a common standard deviation of σ = 1 and a mean difference between intervention arm I and II at δ = 0.5*SD. Further, assuming a significance level of α = 0.05 and a statistical power of 1-β = 0.8 (80%), a total of 204 patients will be recruited in the study which included an extra 10% to compensate for missing data and dropouts.

For secondary outcomes, the observer-perceived patient involvement in SDM (OPTION5) will be used to analyze the audio recordings of the consultations between patient and clinician. A separate sample size calculation was conducted for this outcome; based on a previous RCT study with a mean OPTION5 score of 26.6 in the control arm [31], the calculation of sample size for the OPTION5 measure requires 35 patients in each arm to achieve 80% power (alpha at 0.05) to demonstrate a difference of at least 13.4 points (50% increase in observed level of SDM) [31]. Patients will be consecutively asked for permission to audio record the consultation until the required sample size is achieved; hence, no dropouts or missing data are expected. Therefore, a total of 70 audio recordings are required.

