## Methods and analysis

### Study design

The IMPACTT study is designed as a randomised, controlled trial with two arms in a 1:1 allocation ratio and a primary endpoint of patient-reported involvement in shared decision making. The study protocol is reported following the CONSORT guidelines [21] and registered at ClinicalTrials.gov (NCT05573022).

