### Statistical methods

Data will be stored in a secure server in OPEN Analyse. Descriptive analyses will be performed to explore exchangeability between the two study arms. Data will be presented in a table describing the study population on key characteristics.

The main analyses will be performed as mixed effect models by incorporating the clinician as a random effect. If there is no significant variation, analyses will be performed using linear regression. The 95% confidence intervals will be estimated using bootstrapping. In case of a screwed distribution on key characteristics (non-exchangeability) between the study arms, multivariate analyses will be performed adjusting for potential confounding factors.

Primary and secondary outcomes will be analysed as sum scores and sub scores, and sub-analyses including stratification by sex and age groups. Continuous measures will be presented as mean with standard deviations (SD) or median with interquartile range (IQR) depending on if the findings are normally distributed?. Means will be compared using a 2-sided t-test, medians using a non-parametric K-sample test on the equality of medians. A 2-sided *p*-value of ≤ 0.05 will be used to determine significance.

The consultation length will be measured using the audio recordings and analysed descriptively.

All analyses will be performed as intention-to-treat analyses, and in case a patient did not access the app before consultation, per-protocol analyses will be performed as a sub-analysis. Missing data will be handled according to the scoring instructions of the instruments.

Audio recordings of clinician and patient consultations will be rated by a team consisting of the principal investigator, a second researcher, and two patient representatives. Before rating, an initial calibration between the raters will be performed to avoid inter-observer variation and to reach a scoring consensus. Any discrepancies will be resolved by agreement or a fifth rating. Audio recordings will be stored in a secure server at OPEN.

The team rating the audio recordings will be blinded such that raters will not know which arm the patients were randomised. Overall OPTION scores will be compared using the Wilcoxon-Mann–Whitney two-sample rank-sum test. Inter-rater reliability will be calculated using Interclass Correlation Coefficients (ICC). A reasonable threshold is above 0.6 [36].

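### The stated inputs for the primary sample size give about 141–144 patients, not 204, so inputs and total cannot all be right; the mismatch is conservative

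*Protocol article*

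**What the plan says.** The Sample size section takes its assumptions for the primary outcome from the instrument's user guide: "a common standard deviation of σ = 1 and a mean difference between intervention arm I and II at δ = 0.5*SD". It continues "assuming a significance level of α = 0.05" and sets power at 80%. The result is that "a total of 204 patients will be recruited in the study which included an extra 10% to compensate for missing data and dropouts". The 10% is the only addition named.

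Two further inputs stand elsewhere in the article. Study design describes "two arms in a 1:1 allocation ratio". Statistical methods says "Means will be compared using a 2-sided t-test" and sets a two-sided 5% threshold for significance. The same section plans the main analyses as mixed models with clinician as a random effect, but neither section gives an intraclass correlation or design effect for the sample size.

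**The concern.** A difference of half a standard deviation at two-sided 5% and 80% power is a familiar benchmark that needs a little under 130 patients. A 10% allowance cannot take that to 204. The article gives what reads as a full set of inputs and a total that does not follow from them.

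At stake is the meaning of the primary design statement. A reader of the results will want to know what difference the trial was built to detect, and with what power. As written, either the power, the difference, the SD, the loss allowance or the total is not the one used, or a further input is unreported.

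**Working it through.** **Inputs.** SD σ = 1, difference δ = 0.5 SD, α = 0.05, power 80% and a 10% addition (Sample size); allocation 1:1 (Study design); two-sided testing (Statistical methods).

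**Step 1: evaluable patients.** Normal approximation, per arm:

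n = 2(z₀.₉₇₅ + z₀.₈₀)²σ²/δ² = 2 × (1.960 + 0.842)² / 0.5² = 2 × 7.85 / 0.25 = 62.8, so 63 per arm and 126 in total.

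The exact two-sample t-test gives 63.8, so 64 per arm and 128 in total.

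**Step 2: add 10%** (t-test figures).

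| Method | Total |
|---|---|
| 128 × 1.1 = 140.8 | 141 |
| 64 × 1.1 = 70.4, rounded to 71 per arm | 142 |
| 128 / 0.9 = 142.2 | 143 |
| 64 / 0.9 = 71.1, rounded to 72 per arm | 144 |

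The normal approximation gives 139–140. The stated 204 is not reproduced. The excess is 204 − 144 = 60 to 204 − 141 = 63 patients, that is 60/144 = 42% to 63/141 = 45%.

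**Step 3: other readings.** Totals include the 10%; the ranges cover normal and t calculations and both ways of adding it.

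| Reading | Total |
|---|---|
| One-sided α = 0.05, 80% power | 111–114 |
| Inflation for a rank test | 148–166 |
| Two-sided, 90% power | 188–192 |
| Two-sided, 95% power | 229–234 |
| Two-sided α = 0.01, 80% power | 207–214 |

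For 204 to leave 128 evaluable patients, the loss would have to be 1 − 128/204 = 37%.

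**Step 4: what would give 204.** Only a changed or added input does. A difference of 0.5 points with SD 1.2 gives 92 per arm; 92 × 1.1 = 101.2, rounded to 102, and 2 × 102 = 204. A design effect of about 204/142 = 1.44 would also do it. Both are back-calculated illustrations with no support in the article.

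**Step 5: what 204 delivers if the stated inputs hold.** After 10% loss, 204 × 0.9 = 183.6, about 184 analysed or 92 per arm. By the normal approximation, power for 0.5 SD is Φ(0.5 × √(92/2) − 1.960) = Φ(1.43) = 0.924. The detectable difference at 80% power is 2.802 × √(2/92) = 0.413 SD. The t-test values are:

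| Analysed | Power for 0.5 SD | Difference detectable at 80% power |
|---|---|---|
| 184 (92 per arm) | 92.1% | 0.415 SD |
| 204 (102 per arm) | 94.5% | 0.394 SD |

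**The case against.** The strongest reply is that this is a condensed article and that an input has simply gone unreported. The assumptions are introduced as a list that need not be complete. The planned random effect for clinician shows that the sponsor thought about clustering, and a design effect of about 1.44 would close the gap. This stands in part. It would be tempting to say that clustering cannot be the explanation because patients are individually randomised and share the same oncologists. But the Setting section says only that the oncologists are the same at both sites, and an argument that a design effect is unnecessary does not show that none was used. What the reply does not do is make the passage right: it presents 204 as the result of the listed inputs with 10% as the only addition.

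A second reply is that the error does no harm: more patients mean more power, and a null result would be read mainly from the planned 95% confidence intervals. This also largely stands, and it lowers the severity. It does not make the printed calculation correct.

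**Conclusion.** The point holds as a calculation that its own inputs do not reproduce. They give 141–144 patients; the article states 204, which is 60–63 more. This rests on a two-sided two-sample comparison of means with equal arms, and no variant that keeps the stated effect, α and power comes near 204.

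Three stronger readings are not supported:

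- **That the trial is underpowered.** On the stated inputs it has about 92% power after 10% loss, so the mismatch is conservative.
- **That the stated power and the stated difference are both wrong.** If 0.5 SD stands, the power is understated; if 80% stands, the target difference is larger than the one the trial can detect. The article does not show which applies, or whether the SD, the loss or an unreported design effect is the source.
- **That some 60 patients are being recruited without need.** That follows only if every printed input is the intended one.

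The defect is in reporting and reproducibility. It should be fixed, but it does not threaten the primary comparison.

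**What to change.** Keep 204. First, replace the printed inputs with those actually used (SD, difference, power, loss, and any design effect for clinician with its basis), so that the calculation reproduces.

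If the printed inputs are the intended ones, restate the result instead, for example: 204 randomised, with about 184 analysed after 10% loss, gives about 92% power for a difference of 0.5 SD, or 80% power for about 0.42 SD, at a two-sided 5% level.

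The cost is one or two sentences in the Sample size section. Recruitment, conduct and analysis are unchanged.

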### Data collection

Study data will be collected and managed using the REDCap electronic data capture tool (copyright Vanderbilt University, version 12.0.33 [32]) hosted at OPEN (Open Patient Data Explorative Network, Odense University Hospital, Region of Southern Denmark). After oral consent, patients will be randomised via REDCap and are immediately sent an electronic questionnaire via e-Boks to be answered before the consultation (a total of 13 questions, Patient Q1 in Table 1). E-Boks is a secure national platform for digital, personal mail used by public authorities to citizens. All Danish citizens are required to use e-Boks but can be exempted from use if they fulfil specific requirements. If exempted from use, the patient will receive the questionnaire by mail. In the first questionnaire, enrolled patients give their written, electronic consent to participate and are asked to indicate if they consent to audio recording of the consultation. Patients in intervention arm II will be asked to checkmark if they have accessed and used the digital PtDA and, if not, to state the reason it was not used.

The day after the consultation with the oncologist discussing adjuvant treatment, enrolled patients will receive the second questionnaire from REDCap (a total of 42 questions, Patient Q2 in Table 1). Patients in intervention arm II will also be asked to checkmark if the clinician used the paper-based PtDA during consultation. The patient will receive a reminder to complete the questionnaire after three and six days.

Clinicians will be administered one 9-item questionnaire on paper which they are asked to fill in right after the consultation while they have the consultation fresh in mind (Clinician Q2, Table 1). Clinicians will also be asked if patients in intervention arm II unprovokedly took out their smartphone or tablet during the consultation to use the digital PtDA. Afterwards, answers will be registered manually in REDCap by the principal investigator.

Audio recordings of clinician and patient consultations (N = 70) are collected (Observer Q1, Table 1) for later analysis. The nurse participating in the consultation is responsible for initiating the recording.

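### Audio permission is asked after randomisation, so replacing refusers secures the number of recordings but not the randomised comparison on OPTION5

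*Protocol article*

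**What the plan says.** The Sample size section of the protocol article plans OPTION5 separately from the main trial. Based on "a mean OPTION5 score of 26.6 in the control arm" and a target difference of 13.4 points, it "requires 35 patients in each arm to achieve 80% power", which makes 70 recordings. Permission is sought consecutively until that requirement is met; "hence, no dropouts or missing data are expected".

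The order of events is given under Data collection: "After oral consent, patients will be randomised via REDCap and are immediately sent an electronic questionnaire". In that questionnaire (Patient Q1 in Table 1) patients give written consent to the trial and "are asked to indicate if they consent to audio recording of the consultation". The same questionnaire asks arm II patients whether they have already used the digital aid.

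Statistical methods adds four relevant points:

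- OPTION5 raters are to be blinded to arm.
- Consultation length is measured from the recordings and analysed descriptively.
- Missing data follow the scoring instructions of the instruments.
- "All analyses will be performed as intention-to-treat analyses".

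**The concern.** Replacing people who decline produces the planned number of recordings. It does not produce outcomes for the randomised patients who declined. Because the question comes after allocation, the decision to be recorded can depend on the arm. An arm II patient has by then been invited to the app and may have used it or failed to. Table 1 itself lists not wanting to see the options, lack of time and technical trouble as possible reasons for non-use. Such patients might also be less willing to be recorded and less involved in the consultation. That is plausible, but the article does not establish it.

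At stake is the one outcome with planned blinded rating; the other measures of shared decision making are reported by patients or clinicians who know what was used. With 70 of 204 patients recorded, 134 (66%) have no OPTION5 score and no consultation length. Instrument scoring rules deal with missing items, not with a consultation that was never recorded. Calling these analyses intention-to-treat therefore claims more than the sampling delivers.

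**Working it through.** **Inputs from the article.** 35 per arm, 80% power, alpha 0.05 (two-sided by the general rule in Statistical methods), target difference 13.4 points, 70 recordings, 204 randomised.

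**Assumptions, because the article gives no figure.** The OPTION5 SD, the consent rate in each arm, and the gap in score between consenters and refusers.

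**Step 1: the plan's own figure.** No SD is stated, so 35 per arm cannot be reproduced from stated inputs alone. Solving for the SD:

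SD = 13.4 / [(1.960 + 0.842) × √(2/35)] = 13.4 / 0.670 = 20.0

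Putting SD = 20 back in: n = 2 × (2.802)² × 20² / 13.4² = 35 per arm. The figure is coherent with an SD of about 20, which is used below. The count is not in dispute.

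**Step 2: how consent after allocation enters the contrast.** Let c be the consent rate in an arm and g the mean score of consenters minus that of refusers. The arm's full mean is c × (consenter mean) + (1 − c) × (refuser mean), so the consenter mean exceeds the full mean by (1 − c) × g. The bias in the difference between arms is

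(1 − c₁) × g₁ − (1 − c₂) × g₂

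With the same gap g in both arms this is, in size, the difference in refusal rates × g.

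**Step 3: results (SD 20).**

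| Consent, arm 1 vs arm 2 | Refuser gap | Size of bias | Share of 13.4 |
|---|---|---|---|
| 70% vs 70% | equal, any size | 0 | 0% |
| 80% vs 60% | none | 0 | 0% |
| 80% vs 60% | 0.5 SD | 0.2 × 0.5 × 20 = 2.0 points | 15% |
| 90% vs 60% | 0.5 SD | 0.3 × 0.5 × 20 = 3.0 points | 22% |
| 80% vs 60% | 1 SD | 0.2 × 1 × 20 = 4.0 points | 30% |
| 70% vs 70% | 0.5 SD in one arm, 0 in the other | 0.3 × 0.5 × 20 = 3.0 points | 22% |

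If refusers score lower, the arm with less consent is flattered; if they score higher, the direction reverses. For the 2.0-point case, an SD of 17.5 to 22.5 gives 1.75 to 2.25 points (13% to 17%).

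**Step 4: check with a different model.** Take a normal score with SD 20 and a latent willingness to be recorded that correlates 0.2 to 0.5 with the score. The bias is then correlation × SD × the difference between arms in the inverse Mills ratio. For 80% vs 60% consent the ratios are 0.350 and 0.644, so the bias is 0.294 × 20 × (0.2 to 0.5) = 1.2 to 2.9 points. The two-sided type I error becomes 0.057 to 0.094 in place of 0.05. Equal consent again gives zero. The two models agree on the order of size.

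**The case against.** The strongest reply is that the sentence stands in a sample-size section, next to the 10% added to the main sample for missing data and dropouts, and only explains why 70 is not inflated. In that sense it is right. The article does not claim that recorded patients represent all those randomised. The bias is also hypothetical: the article gives no consent rate, no difference between arms and no refuser gap. These points stand and limit the finding. They do not answer it, because the order of randomisation and permission is stated in the article and is not a detail left to an analysis plan.

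A reader might infer more than the documents support:

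- *That stopping at 70 fails to secure 35 per arm.* The stated requirement is per arm, and 70 is its sum. Even a 27/43 split would lower power only from 80% to about 78%.
- *That filling the quota early in enrolment biases the comparison.* Allocation is 1:1 in blocks of 4 or 6, so both arms are sampled over the same period. At most this touches representativeness.
- *That selective consent would go unseen.* Audio permission is an answer in a questionnaire managed in REDCap, so refusals by arm can be retrieved.
- *That consultation length faces a false-positive test.* It is only described; the problem there is a self-selected estimate.

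It may also be said that moving the question does not help, since written consent to the trial is itself given after randomisation and a patient can withdraw a telephone agreement. This is partly right and is reflected in the fix.

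**Conclusion.** The point holds in a limited form. Replacement makes it reasonable not to inflate 70. It does not make the OPTION5 data complete, and it does not preserve the randomised comparison, because permission is asked after allocation of patients who are not blinded. The intention-to-treat label does not fit OPTION5 or consultation length.

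The documents do not show that the OPTION5 result will be biased. The range starts at zero, with equal consent and equal refuser gaps. It is about 2 points (15% of the target difference) under 80% versus 60% consent, a 0.5 SD gap and a back-solved SD of about 20. The more extreme assumptions shown reach 4 points. The primary outcome is not affected. This is a cheap improvement to a secondary outcome and worth making because OPTION5 is the only one with blinded rating.

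**What to change.** 1. Ask for audio permission in the recruitment telephone call, before the REDCap randomisation, and confirm it in the first questionnaire. Form the OPTION5 set from patients who agreed before allocation. Knowledge of the arm then cannot drive entry to the set.
2. Limit the sentence on dropouts and missing data to what replacement achieves, namely reaching the required number of recordings.
3. Describe OPTION5 and consultation length as analyses of a consenting subset rather than as intention-to-treat. Report later refusals and failed recordings by arm.

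The cost is one more question in a call that already takes place, some rewording and a short table. The call becomes slightly longer. Some patients will still withdraw permission later and some recordings will fail; these remain as missing data within a set fixed before allocation, and are visible by arm. If recruitment is too far on for item 1, items 2 and 3 still apply, with all refusals counted by arm.

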### Data collection

Study data will be collected and managed using the REDCap electronic data capture tool (copyright Vanderbilt University, version 12.0.33 [32]) hosted at OPEN (Open Patient Data Explorative Network, Odense University Hospital, Region of Southern Denmark). After oral consent, patients will be randomised via REDCap and are immediately sent an electronic questionnaire via e-Boks to be answered before the consultation (a total of 13 questions, Patient Q1 in Table 1). E-Boks is a secure national platform for digital, personal mail used by public authorities to citizens. All Danish citizens are required to use e-Boks but can be exempted from use if they fulfil specific requirements. If exempted from use, the patient will receive the questionnaire by mail. In the first questionnaire, enrolled patients give their written, electronic consent to participate and are asked to indicate if they consent to audio recording of the consultation. Patients in intervention arm II will be asked to checkmark if they have accessed and used the digital PtDA and, if not, to state the reason it was not used.

The day after the consultation with the oncologist discussing adjuvant treatment, enrolled patients will receive the second questionnaire from REDCap (a total of 42 questions, Patient Q2 in Table 1). Patients in intervention arm II will also be asked to checkmark if the clinician used the paper-based PtDA during consultation. The patient will receive a reminder to complete the questionnaire after three and six days.

Clinicians will be administered one 9-item questionnaire on paper which they are asked to fill in right after the consultation while they have the consultation fresh in mind (Clinician Q2, Table 1). Clinicians will also be asked if patients in intervention arm II unprovokedly took out their smartphone or tablet during the consultation to use the digital PtDA. Afterwards, answers will be registered manually in REDCap by the principal investigator.

Audio recordings of clinician and patient consultations (N = 70) are collected (Observer Q1, Table 1) for later analysis. The nurse participating in the consultation is responsible for initiating the recording.

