**Fig. 1 Fig1:**
[figure not shown]
Recruitment procedure flow diagram with eligibility, interventions and data collection. Q: Questionnaire. O: Observer measure. PI: Principle investigator

The principal investigator telephones the eligible patients, identified by the study nurse, to obtain oral consent and randomise them. Randomisation will be performed as block randomisation with an equal allocation ratio (1:1) using a computer-generated table of block sizes of 4 or 6, created and supervised by a data manager at OPEN, Open Patient Data Explorative Network, Odense University Hospital, Region of Southern Denmark.

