### Interventions

Intervention arm I will be introduced to a paper-based PtDA by the clinician in the consultation. Participants in intervention arm II will be invited to access the digital PtDA via an app before the consultation. The paper-based PtDA will not be used during consultation in intervention arm II. Both arms will be exposed to the same PtDA in terms of the lexical, visual and structural content, only the format (digital versus paper-based) is different.

The PtDA used in this study is based on the generic patient decision aid template developed and clinically tested by the Center for Shared Decision Making, Vejle Hospital, Denmark and based on the International Patient Decision Aid Standards (IPDAS) [22]. The PtDA is customised for use by patients with early-stage breast cancer who went through curative surgery. The PtDA specifically indicates the decision about having none, one or more adjuvant treatments depending on the patient's value assigned to survival rates, side effects, long-term consequences, and quality of life. The PtDA involves a five-step procedure to make explicit clarification of the patient’s values for adjuvant treatment and presents options A) chemotherapy, B) radiation, C) hormone therapy, D) antibody therapy, and E) no treatment including benefits and harms of each option, outcome probabilities, and personal stories describing experiences of others that are relevant to the decision at hand. The options offered to the patient depend on the patient’s age and tumor characteristics. The paper-based version has been available for use during consultations in the clinic since 2017 [23].

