### Outcomes

The primary outcome is the extent to which patients are involved in a shared decision making process reported by the patient using the SDM Process_4 questionnaire [24]. This instrument has four items and demonstrated good acceptability with high response rates and very low missing data. In a national study of 10 different medical conditions, the SDM Process_4 did not show floor or ceiling effects. Calculations showed moderate to good reliability (ranging from 0.54 to 0.87), and retest reliability was moderate (0.64). The construct validity assessment indicated that higher scores correlated with better decision quality and that patients were less likely to think they had made the wrong decision [24].

Secondary outcomes, using well tested instruments, are the patient-perceived level of SDM [25], patient engagement [26], preparation for decision making scale [12], decisional conflict scale [7], and Control preferences Scale [27]. Additional secondary outcomes are consultation length, clinician-perceived level of SDM [28], and observer-perceived patient involvement in SDM [29, 30]. All questionnaires are validated and translated into Danish (see Table 1 for further details). Patients’ demographic characteristics will include age, gender, education, occupation, and living arrangements.

**Table 1 Tab1:** Content of data collection outcome measures

Distribution	Measurement instrument	Description	Item no., range and scoring
Patient Q1	Decisional Conflict Scale [7]	Patient-reported perceived measure of four of five dimensions of decisional conflict (e.g., uncertainty, uninformed, unclear values, unsupported)	12 items 5 point Likert scale (0–4) Mean standardized score*25 (0–100)
	Control Preference Scale [27]	Patient-reported preference for the patient’s preferred role in shared decision making	1 item with five statements (pick one)
	Access to digital PtDA	Patients in intervention arm II are asked if they have accessed and used the digital PtDA	Yes/No – if no, to state the reason: • Cannot install the app • Cannot open the PtDA in the app • Problems with e-Boks • Other technical issues • Did not have the time • Do not want to see the options • Other cause / do not know
Patient Q2	Shared Decision Making Process 4 (SDM Process_4) [24]	Patient-reported engagement	4 items 4 point Likert scale (0–1, yes/no) Points are summed (0–4)

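### The only patient question on pre-consultation app use is in a form sent straight after randomisation, so later app users can be recorded as non-users in the per-protocol sub-analysis

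*Protocol article*

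**What the plan says.** Recruitment procedure: the principal investigator telephones eligible patients "to obtain oral consent and randomise them". Data collection continues: "patients will be randomised via REDCap and are immediately sent an electronic questionnaire via e-Boks to be answered before the consultation". No narrower time for completing this first questionnaire is given.

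The first questionnaire carries several things at once. Table 1 lists the Decisional Conflict Scale, the Control Preference Scale and the app-access item under Patient Q1. The last of these is described as "Patients in intervention arm II are asked if they have accessed and used the digital PtDA", answered Yes or No, with a list of reasons if No. Data collection repeats it: "Patients in intervention arm II will be asked to checkmark if they have accessed and used the digital PtDA". The same form takes consent: "In the first questionnaire, enrolled patients give their written, electronic consent to participate and are asked to indicate if they consent to audio recording".

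Exposure runs up to the consultation. Under Interventions, "Participants in intervention arm II will be invited to access the digital PtDA via an app before the consultation". Eligibility criteria explains that patients are telephoned beforehand so that the digital arm has time to use the app, and excludes patients with less than 24 hours between the final surgical and first oncology consultations.

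Statistical methods states "All analyses will be performed as intention-to-treat analyses", and adds a per-protocol sub-analysis where a patient did not access the app before the consultation.

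**The concern.** The status the per-protocol analysis needs is whether the app had been used by the start of the consultation. The status collected is whether it had been used by the time the patient filled in a form that arrives at the start of the exposure window. For anyone who answers promptly these are different questions, and prompt answering is a natural response to a form sent at once.

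If true users are recorded as non-users, the per-protocol set in arm II is too small. If prompt answerers differ from others in engagement or health literacy, it is also selectively composed. The recorded reasons for non-use suffer too: a patient who ticks lack of time on receipt may have had time later. App uptake is an important descriptive result in a trial of a digital tool, and it would be understated.

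A smaller matter arises from the same form. Written consent and consent to audio recording are given after allocation, so a decision to decline either could depend on the arm.

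**Working it through.** **1. Sequence.**

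1. Telephone call: oral consent, then randomisation (Recruitment procedure, Data collection).
2. Patient Q1 sent immediately, answerable until the consultation (Data collection).
3. Arm II can use the app until the consultation (Interventions, Eligibility criteria).
4. Consultation.
5. Clinician form right after the consultation (Data collection).
6. Patient Q2 sent the day after the consultation (Data collection).

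The access answer is fixed at some moment between steps 2 and 4, but the analysis needs the status at step 4. A Yes given early stays correct. A No given early stays correct only if the app is never opened afterwards. Misclassification is therefore in one direction, from user to non-user.

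**2. Could another item correct an early No?** Table 1 offers two further exposure items for arm II. Patient Q2 asks whether the clinician showed the paper version. The clinician form asks whether the patient took out a device during the consultation. Neither asks about app use before the consultation, and no other source, such as app usage records, is described.

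**3. Size.** The documents give no figure for how many patients answer early, so this is an illustration.

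- Arm size: 204 / 2 = 102. After the plan's 10% allowance, 102 × 0.9 = 91.8, about 92.
- Assumptions: a share *e* of arm II answers Q1 before opening the app, and a share *u* of those opens it later. Wrongly classified = 92 × *e* × *u*.
- *e* = 0.2 to 0.3 with *u* = 1: 92 × 0.2 = 18.4 and 92 × 0.3 = 27.6, so 18 to 28 patients. This is the upper bound for that *e*.
- Same *e* with *u* = 0.5: about 9 to 14.
- *e* = 0 or *u* = 0: none.

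If a share *m* of true users is wrongly removed and scores *d* differently from the rest, the arm II per-protocol mean shifts by *m* × *d*. With *m* = 0.2 to 0.3 and an assumed *d* of 0.5, the shift is 0.10 to 0.15 on a scale with planned SD 1. With *d* = 0 it is zero and only precision is lost.

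**4. Secondary point: refusal after allocation.** No rate of written refusal is given. If 10% of arm II were lost, would have scored 0.5 lower, and arm I had no matching loss, the arm II mean would move by 0.10 × 0.5 = 0.05. That is 0.05 / 0.5 = 10% of the design difference. With equal and similar loss in both arms the effect on the comparison cancels.

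Power is not the issue. With 102 per arm, difference 0.5, SD 1, two-sided 5% and 10% loss in arm I, normal-approximation power is 92, 91, 89 and 86% for arm II losses of 10, 20, 30 and 40%. For example, at 10% loss in both arms: 0.5 / √(2/91.8) − 1.96 = 1.43, giving 92%. These powers take the recruited 204 as given. The stated inputs alone require only 63 per arm (126 in total, about 140 with the 10% allowance), which is a separate matter.

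**The case against.** The strongest reply is that little depends on this item. It does not enter the intention-to-treat analysis, and the per-protocol analysis is explicitly a sub-analysis. The article does not say in so many words that the Q1 answer defines the per-protocol set. Patients may answer shortly before the consultation, and instructions on timing may sit in the questionnaire, which is not shown. All of this is fair and limits the weight of the point. It does not remove it: the Q1 item is the only described source of pre-consultation access, and the stated instruction allows an answer at any time before the consultation.

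A reader might infer more than the documents support:

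- *That patients consent only after learning their arm.* Oral consent comes before randomisation. Only written and audio consent follow. Arm II knows its arm from the app invitation, but the text does not say that arm I is told before returning Q1.
- *That this contradicts the intention-to-treat statement.* Nothing says that patients who do not return Q1 are removed, and their handling may be set out in the full protocol or analysis plan.
- *That refusal biases the comparison.* No passage shows refusal differing by arm. It is a risk only.
- *That Q1 scores are misused as a baseline.* The plan never calls them a baseline and does not adjust for them. Measuring them after allocation is not in itself an error.

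**Conclusion.** The point holds for the app-access item. It is collected too early to establish access up to the consultation, the error can only turn users into non-users, and no described item repairs it. It affects the per-protocol sub-analysis and the reporting of app uptake, and leaves the intention-to-treat primary analysis untouched. The figure of 18 to 28 out of about 92 is an upper-bound illustration: it assumes 20 to 30% early answering and later use by every early answerer, neither of which the documents support or exclude. The conclusion also rests on the reasonable inference that the Q1 item is what determines per-protocol status.

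Consent to participation in writing and to audio recording after allocation is a secondary matter for transparent reporting. It is not a demonstrated bias.

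**What to change.** Move the app-access item and its list of reasons to Patient Q2, or repeat them there, worded to ask about use before the consultation so that later use is not counted. Define per-protocol status from that answer.

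The cost is a small change to the REDCap forms, slightly later recall, and no access answer from patients who do not return Q2. The last matters little for outcomes collected in Q2, including the primary outcome, because those patients have no outcome data either. For observer and clinician outcomes the Q1 answer, if the item is kept there too, can serve as back-up.

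For the secondary point, count every randomised patient by arm and report written non-consent and audio non-consent by arm, with reasons where given. This needs no change in procedure.

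Randomising only after electronic consent is not required. It would shorten the time for app use that the 24-hour rule is meant to protect, and it would not work for patients exempt from e-Boks, who receive the form by mail.
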